### Participant recruitment and informed consent

Informed verbal consent will be obtained from village leaders and representatives for household level data collection. At the household level, fieldworkers will provide information about the study objectives and data collection requirements, including how long the survey will take, the measurements needed and potential risks, to each individual in Hausa or their preferred language. Informed written consent will then be obtained from the head of household or another adult representative, following which informed written consent will be obtained from each adult participating in the study and from an adult for each child participating in the study. Each individual must provide a signature or written mark on the consent form to prove their willingness to participate. Households and individuals will not be pressurised to participate and it will be made clear that participation or non-participation will not affect their entitlement to humanitarian or any other forms of assistance. Participants will also be given general information about the interventions to which they have been allocated or an explanation if they have not been targeted, with advice to contact Concern Worldwide staff for more information if required.

For the focus group discussions for the cost-effectiveness analysis, a standardised text will be read aloud and informed verbal consent will be obtained from participants at the start of each discussion. It will be made clear that their participation and any information they volunteer will not affect their eligibility for the ongoing programme nor any potential future programmes. For key informant interviews, the purpose of the study will be explained prior to starting the interview and informed verbal consent will be obtained.

### Data collection

Data collection plans are illustrated in Fig. 2. Quantitative data collection from the cohort will take place at two time points, in March-April before the intervention and after the intervention in September-October. Trained staff will collect data under the supervision of a study coordinator and field manager. We will use structured questionnaires administered to the head of household, women of childbearing age (15–49 years) and mothers or carers of eligible children. Questionnaire tools will be developed using standard indicators, and refined based on the results of formative research and piloting. Data will be collected using Digital Data Gathering devices.

Qualitative data collection to describe the context and explore mechanisms by which the interventions work or fail to work will involve a longitudinal study of a purposively selected sample of cash receiving and non-cash receiving households, and additional, topic-focused qualitative studies. Data will be collected using interviews, focus group discussions and observation notes. Interviews and discussions will be recorded and a purposive sample transcribed and translated. Researchers will write descriptive reports of data that is not transcribed. The compilation of routine quantitative monitoring data, collected by Concern Worldwide during the intervention period from April to September, will help us to describe the study context and how this changes over time, and will allow for evaluation of the interventions’ implementation.

For cost-effectiveness analysis, institutional costs will be assessed using accounting data and information collected from key informant interviews and programme documentation. Societal and households costs will be assessed using qualitative data collected from focus group discussions and quantitative data collected from the cohort. Data collection for the cost-effectiveness analysis will be conducted by a separate study team including an international researcher and a translator, and a note-taker during community-level discussions.

### Outcome measures

The primary outcome measure is the prevalence of global acute malnutrition (weight for height < −2 Z-scores (WHO 2006 growth standards) and/or nutritional oedema) in children aged 6–59 months. Secondary outcomes measures are 1. Prevalence of global acute malnutrition (MUAC <12.5 cm and or nutritional oedema in children 6–59 months), 2. Mean weight for height (WHO 2006 growth standards) in children 6–59 months, 3. Mean MUAC in children 6–59 months, 4. Mean haemoglobin concentration in children 6–59 months, 5. Prevalence of anaemia in children 6–59 months, 6. Mean haemoglobin concentration in women aged 15–49 years, 6. Prevalence of anaemia in women aged 15–49 years, 8. Household Dietary Diversity Score, 9. Individual Dietary Diversity Score in children 6–59 months, 10. Individual Dietary Diversity Score in women 15–49 years, 11. Household expenditure and multidimensional poverty, 12. Cost effectiveness of the modified cash intervention.

### Measurement instruments

The weight of the children and women will be measured using an electronic scale measuring to 0.1 kg precision. Length (for children <24 months of age) and height (for children ≥24 months of age and women) will be measured using a baby mat and/or stadiometer measuring to 0.1 cm precision. MUAC will be measured on the left arm using an insertion tape to 0.1 cm precision. Bilateral pitting oedema will be assessed through applying medium pressure on the dorsum of both feet with thumbs for three seconds and determining presence/absence of an indentation. Haemoglobin concentration will be measured using the HemoCue 301 analyser to 0.1 g/dL precision.

### Standardisation procedure

Enumerators will be trained in anthropometric measurements and standardisation tests will be undertaken to assess the precision and accuracy of their measurements. Plausibility checks will be run on each team’s data using the software Emergency Nutrition Assessment [27], to examine the quality of the data and determine need for intensive retraining and closer supervision. Digital scales will be checked for accuracy daily using known weights. Structured questionnaires will be standardised and piloted prior to finalisation. Training of enumerators will ensure complete understanding of the questions in French and their appropriate translation in to Hausa. Qualitative fieldworkers will be hired for their skills and experience in collecting qualitative data and will be trained and supervised by an experienced qualitative researcher.

### Sample size calculation

In order to detect a difference of 5 percentage points in the prevalence of acute malnutrition among children 6–59 months of age between the trial arms, assuming a fixed number of 20 clusters and end-line prevalence of 21 %, and allowing a type 1 error rate of 5 % and power of 80 %, we calculated that a minimum sample size of 1,767 children in 10 clusters for each arm will be necessary. Because the clustered sample design will induce correlation within sampling units, we used a sample size calculation method designed for use with clustered RCTs [28]. We also accounted for variable numbers of children served by each distribution point in calculating our final sample size.

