**Methods/design:**

This cluster-randomised controlled trial will compare two types of unconditional cash transfer for ‘very poor’ households in ‘vulnerable’ villages defined and identified by the implementing organisation. 3,500 children (6–59 months) and 2,500 women (15–49 years) will be recruited exhaustively from households targeted for cash and from a random sample of non-recipient households in 40 villages in Tahoua district. Clusters of villages with a common cash distribution point will be assigned to either a control group which will receive the standard intervention (*n* = 10), or a modified intervention group (*n* = 10). The standard intervention is 32,500 FCFA/month for 4 months, June to September, given cash-in-hand to female representatives of ‘very poor’ households. The modified intervention is 21,500 FCFA/month for 5 months, April, May, July, August, September, and 22,500 FCFA in June, providing the same total amount. In both arms the recipient women attend an education session, women and children are screened and referred for acute malnutrition treatment, and the households receive nutrition supplements for children 6–23 months and pregnant and lactating women. The trial will evaluate whether the modified unconditional cash transfer leads to a reduction in acute malnutrition among children 6–59 months old compared to the standard intervention. The sample size provides power to detect a 5 percentage point difference in prevalence of acute malnutrition between trial arms. Quantitative and qualitative process evaluation data will be prospectively collected and programme costs will be collected and cost-effectiveness ratios calculated.

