### Study design and randomisation

The study design is a community-based, two-arm cluster RCT. We will assess the impact of UCT interventions on the risk of child undernutrition among households targeted for intervention and also in the community in which the interventions are implemented. A clustered design is necessary to ensure feasibility of delivery of the interventions being tested and to prevent contamination. The unit of randomisation will be the cash distribution point; i.e. one or more villages grouped to receive cash in a given location. Households will be assigned to the trial arm on the basis of their village of residence. The randomisation will be undertaken in a public meeting to which the village leaders will be invited. The names of the villages and their cash distribution point will be written on pieces of paper placed in sealed envelopes of identical shape size and colour. Meeting participants will be invited to blindly select envelopes one by one which will be sequentially allocated to the modified and standard cash arms, until all have been allocated. There will be around 20 cash distribution points, which will result in each intervention group having 10 clusters that will contain around 20 villages.

Cash receiving households will be exhaustively sampled from the selected villages for inclusion in the study cohort. In addition, a sample of households not eligible for cash transfers will be randomly sampled for inclusion in the cohort, from the same villages. The study participants will be children 6–59 months and women 15–49 years, exhaustively sampled from the selected households. The target number of participants is 3,500 children (6–59 months) and 2,500 women (15–49 years). Disabled and seriously sick individuals will be excluded.

Questions related to household costs and income will be included in the endline cohort questionnaire. For collection of qualitative data on household and community costs, up to 10 villages will be selected purposively using selection criteria (e.g. village size, whether village is located at a distribution point, remoteness of village, receipt of standard or modified intervention) to ensure a wide range of village characteristics are represented in the sample. Up to nine participants for the focus group discussions will then be selected randomly from amongst the programme beneficiaries in each village.

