### Data analyses

We will test for an end-line difference in the prevalence of acute malnutrition, among children 6–59 months, between the cash receiving households in the two study arms. Analysis will be conducted using generalized estimating equations (GEE) and adjusted for correlation of responses within clusters. We will choose our covariates and identify potential confounders using the pathways described in the theory of change (Fig. 1), and explore the intervention’s mechanisms of action. We will also undertake post hoc analyses by age strata, <24 months and ≥24 months. We will also test for an end-line difference in acute malnutrition prevalence between non-beneficiary households in the two arms of the trial, to assess the impact of the modified intervention at a population level.

Formative research data about context will be synthesized into a narrative report, which will be updated as contextual changes occur. Qualitative data from the longitudinal and focused studies will be analysed using descriptive content analysis, comparing views from different participants within each intervention group in the trial and members of non-cash receiving households to assess the extent of triangulation and explore how the intervention receipt affected different participants. Researchers will discuss emergent themes, and coding structures will be developed from these themes and from the research questions. Data will then be coded in NVivo V10. Data will be summarised and described using illustrative quotes. Longitudinal qualitative data collection will be analysed between data collection points, to build our theory of how the intervention is working or not working. We will discuss and validate the development of our theory of change and research findings with a sample of research participants and team members at two time points, one during the intervention implementation, and one after the UCT has ceased.

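### The 3,500-child target mixes cash recipients and non-recipients, but the test of hypothesis 1 uses recipients only and needs 1,767 per arm, so the target does not support the stated power

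*Protocol article*

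**What the plan says.** Four statements in the protocol article bear on this point.

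- **Required number.** The Sample size calculation section begins "In order to detect a difference of 5 percentage points in the prevalence of acute malnutrition" and continues "assuming a fixed number of 20 clusters and end-line prevalence of 21" per cent, "allowing a type 1 error rate of 5 % and power of 80" per cent. It concludes that "a minimum sample size of 1,767 children in 10 clusters for each arm will be necessary".
- **Target number.** Under Study design and randomisation: "The target number of participants is 3,500 children (6–59 months"). The same section takes all cash-receiving households in the selected villages and adds that "a sample of households not eligible for cash transfers will be randomly sampled for inclusion in the cohort". The Methods/design part of the abstract likewise describes the 3,500 as drawn from both kinds of household.
- **Analysis population.** The Data analyses section tests the end-line difference "among children 6–59 months, between the cash receiving households in the two study arms". It then describes a second, separate test between non-beneficiary households, for the population-level question. These correspond to hypotheses 1 and 2. No test on the two groups pooled is described.
- **Power claim.** The abstract says: "The sample size provides power to detect a 5 percentage point difference in prevalence of acute malnutrition between trial arms".

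The Discussion explains how non-recipients came to be in the cohort: a separate cross-sectional survey had been planned, and a sample of non-recipient households was put into the cohort in its place. The article neither gives the split between the two groups nor shows that the sample size was revisited after that change.

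**The concern.** The required number, the target number and the analysis population do not fit together. If 1,767 children per arm are needed for a test, they must be in that test. A total of 3,500 is about enough for one comparison of that size, but the article spreads it over two groups that are analysed separately. Every non-recipient child counted in the 3,500 is a child missing from the recipient comparison.

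What is at stake is how a null result on hypothesis 1 would be read. The abstract invites the reader to take the trial as adequately powered for 5 points among targeted households. If the recipient number is well below 1,767 per arm, failing to find a difference says less about a 5-point effect than that sentence implies. The type I error and the validity of the estimate are not affected.

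**Working it through.** **1. The contradiction, from stated figures only.** Required: 2 × 1,767 = 3,534 children in the comparison. Targeted: 3,500, or 3,500 / 2 = 1,750 per arm if split equally, recipients and non-recipients together. Tested under hypothesis 1: recipients only. With any appreciable non-recipient sample inside the 3,500, the recipient comparison has materially fewer than 1,767 per arm. This step needs no ICC and no assumed share.

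**2. Can 1,767 be reproduced?** Inputs from the Sample size calculation section: type I error 5% (two-sided assumed), power 80%, difference 5 points, prevalence 21%, 10 clusters per arm. The section does not say which arm has 21%, so both 21% v 16% and 26% v 21% are carried. Without clustering, with p̄ the mean of the two prevalences:

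n = [1.96 √(2p̄(1−p̄)) + 0.8416 √(p₁(1−p₁) + p₂(1−p₂))]² / 0.05²

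- 21% v 16%: (1.96 × 0.5491 + 0.8416 × 0.5480)² / 0.0025 = 946 per arm.
- 26% v 21%: (1.96 × 0.5996 + 0.8416 × 0.5986)² / 0.0025 = 1,128 per arm.

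The article gives no ICC or cluster-size variation, so 1,767 cannot be derived independently, but the design effect it implies can be. With 1,767 / 10 = 176.7 children per cluster and design effect = 1 + (176.7 − 1) × ICC:

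- 21% v 16%: 1,767 / 946 = 1.868, so ICC = 0.868 / 175.7 = 0.0049.
- 26% v 21%: 1,767 / 1,128 = 1.566, so ICC = 0.566 / 175.7 = 0.0032.

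So 1,767 is attainable from the stated inputs with a small ICC. Allowing for unequal clusters lowers the implied ICC (0.0040 and 0.0026 at a cluster-size coefficient of variation of 0.5) but leaves the powers below unchanged, because the ICC is recalibrated to give 80% at 1,767.

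**3. Power at smaller recipient numbers.** The recipient share s is an assumption. Set N = 1,750 × s per arm, m = N / 10 and n_eff = N / [1 + (m − 1) × ICC]; then

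power = Φ{[0.05 √n_eff − 1.96 √(2p̄(1−p̄))] / √(p₁(1−p₁) + p₂(1−p₂))}

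Worked case, s = 60%, 21% v 16%: N = 1,050, m = 105, design effect 1 + 104 × 0.00494 = 1.514, n_eff = 694, and power = Φ[(0.05 × 26.34 − 1.0763) / 0.5480] = Φ(0.439) = 67.0%.

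| Assumed recipient share | Recipients per arm | Power, 21% v 16% | Power, 26% v 21% |
|---|---|---|---|
| 100% | 1,750 | 79.8% | 79.8% |
| 80% | 1,400 | 74.7% | 73.7% |
| 70% | 1,225 | 71.2% | 69.7% |
| 60% | 1,050 | 67.0% | 64.8% |
| 50% | 875 | 61.6% | 58.8% |
| 40% | 700 | 54.8% | 51.4% |

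The direction of the 21% assumption makes little difference. The recipient share drives the result.

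**The case against.** The strongest reply is that 3,500 may be a recipient-only figure. It lies close to 3,534, and the Discussion says non-recipients were first to be covered by a separate survey. The target could have been set before that change and carried over without re-labelling. The power statement would then stand and the headcount wording would be at fault. This is plausible and cannot be ruled out, and it changes which text needs correcting. It does not remove the inconsistency, because the abstract and the design section, as they now read, both include non-recipients in the 3,500.

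A second reply is that 3,500 is a target and that recipient households are sampled exhaustively, so the recipient number is not capped and could exceed what the target implies. That also stands. A reader might infer that the trial failed to reach its power; the article gives no recipient count and does not support that.

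Three further readings are tempting and should be resisted.

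- The gap of 3,534 − 3,500 = 34 children might be taken as a shortfall in itself. It is rounding: power at 1,750 per arm is 79.8%.
- A reader might re-run the power with a t reference on 18 degrees of freedom and report a larger loss. That takes an ICC calibrated to a normal reference and then changes the reference. With the ICC recalibrated to the t reference, power is 79.8% on the full 3,500 and about 66% at a 60% share, close to the figures above.
- The article states no allowance for loss to follow-up, no ICC or cluster-size variation, and no power for the non-recipient test. A condensed article commonly leaves these to the full protocol, so their absence is not evidence of a fault.

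**Conclusion.** The inconsistency is established by the article's own figures: the required number, the target and the population of the first test cannot all hold as written. The abstract's claim of power for a 5-point difference is therefore unsupported by the stated target for hypothesis 1. The Data analyses section does not call the recipient comparison primary, but that comparison comes first and matches both hypothesis 1 and the primary outcome.

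The size is much less certain. It rests on an assumed recipient share, equal arms, a two-sided test and an ICC back-solved from 1,767, so the table is a scenario range and not an estimate. A reader might conclude that the trial had a large chance of missing a true 5-point effect. That fits the lower shares, but at an 80% share the loss is only about 5 to 6 points of power.

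**What to change.** State the target numbers of recipient and non-recipient children separately, and bring the abstract and the Study design and randomisation, Sample size calculation and Data analyses sections into agreement. What follows depends on the recipient number:

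- **Fewer than 1,767 recipients per arm:** restate the power, or the difference detectable with 80% power, for the recipient comparison at that number, both in the Sample size calculation section and in the abstract.
- **3,500 was meant as recipients only:** correct the abstract and the design section to say so, and give the non-recipient number in addition.

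The cost is a few sentences and at most one recalculation. No extra enrolment is needed. The only downside is that the stated power may turn out less favourable.

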### Data analyses

We will test for an end-line difference in the prevalence of acute malnutrition, among children 6–59 months, between the cash receiving households in the two study arms. Analysis will be conducted using generalized estimating equations (GEE) and adjusted for correlation of responses within clusters. We will choose our covariates and identify potential confounders using the pathways described in the theory of change (Fig. 1), and explore the intervention’s mechanisms of action. We will also undertake post hoc analyses by age strata, <24 months and ≥24 months. We will also test for an end-line difference in acute malnutrition prevalence between non-beneficiary households in the two arms of the trial, to assess the impact of the modified intervention at a population level.

Formative research data about context will be synthesized into a narrative report, which will be updated as contextual changes occur. Qualitative data from the longitudinal and focused studies will be analysed using descriptive content analysis, comparing views from different participants within each intervention group in the trial and members of non-cash receiving households to assess the extent of triangulation and explore how the intervention receipt affected different participants. Researchers will discuss emergent themes, and coding structures will be developed from these themes and from the research questions. Data will then be coded in NVivo V10. Data will be summarised and described using illustrative quotes. Longitudinal qualitative data collection will be analysed between data collection points, to build our theory of how the intervention is working or not working. We will discuss and validate the development of our theory of change and research findings with a sample of research participants and team members at two time points, one during the intervention implementation, and one after the UCT has ceased.

Cost-effectiveness analysis will combine quantitative and qualitative data on institutional, beneficiary, and community-level costs to estimate total intervention costs from a societal perspective. The analysis will be done using Microsoft Excel and TreeAge software packages. Community-level qualitative data will be analysed for themes related to the opportunity cost of participation and resources required to access the program. An activity-based cost analysis will be conducted, allocating and estimating costs per major program activity using staff time allocation proportions. Cost-effectiveness will be assessed using incremental cost-effectiveness ratios (ICER), representing the additional cost per successful outcome achieved (e.g. case of acute malnutrition averted) by the modified relative to the standard intervention. Additional costing metrics will be calculated, including cost per beneficiary and cost-transfer ratio. Sensitivity analyses will be conducted to gauge whether plausible changes in various study parameters would result in significant changes in the base case cost-effectiveness outcomes.

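### The primary end-line model does not fix baseline nutritional status as a covariate, although the cohort is measured before the intervention and about 20 clusters are allocated without described restriction

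*Protocol article*

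**What the plan says.** All references are to the protocol article.

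- **Data analyses.** The primary test is worded "We will test for an end-line difference in the prevalence of acute malnutrition" among children aged 6–59 months, between cash-receiving households of the two arms. The method is GEE with allowance for within-cluster correlation. The section adds that covariates and potential confounders will be chosen from the theory-of-change pathways, and links this to exploring mechanisms. It names no covariate.
- **Data collection.** The cohort is surveyed twice, "in March-April before the intervention and after the intervention in September-October".
- **Study design and randomisation.** Around 20 distribution points are allocated in a public meeting: "Meeting participants will be invited to blindly select envelopes one by one", with envelopes assigned in sequence to the two arms. No stratification, matching or other restriction is described. The target of 3,500 children covers recipient and non-recipient households together.
- **Sample size calculation.** The target difference is 5 percentage points, "assuming a fixed number of 20 clusters and end-line prevalence of 21" per cent and "allowing a type 1 error rate of 5 % and power of 80" per cent. The result is "a minimum sample size of 1,767 children in 10 clusters for each arm will be necessary". No ICC or cluster-size variation is given.
- **Ethical considerations.** The safety test on MUAC is the one analysis with named adjusters: cluster, age and sex.

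**The concern.** In a before-and-after cohort, a child's own earlier weight-for-height is an obvious candidate for explaining later wasting, and it is already collected. A primary model that omits it leaves usable precision behind. It also offers no adjustment if the draw happens to place more wasted children in one arm, which can happen to a material degree with 10 clusters per arm and unrestricted allocation.

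The covariate sentence adds a second difficulty. It draws adjusters from the pathways through which the intervention is meant to act. Variables on those pathways measured after allocation are mediators, and adjusting for them would change the effect being estimated. Leaving the choice open also leaves discretion over the primary model until data are available.

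**Working it through.** **Inputs from the article:** 5-point difference, 21% prevalence, 5% error, 80% power, 10 clusters and 1,767 children per arm, and a recruitment target of 3,500 children (1,750 per arm).

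**Assumptions, not in the article:** a two-sided test; 21% v 16% (the article does not say which arm has 21%); equal clusters; the ICC ρ; the correlation r between a child's baseline and end-line weight-for-height z-score; baseline prevalence of 12% to 21%.

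**1. The plan's own figure.** For 21% v 16% without clustering, n = 946 per arm. The implied design effect is 1,767/946 = 1.87. With 176.7 children per cluster, ρ = (1.868 − 1)/175.7 = 0.0049. With 26% v 21%, n = 1,128, the design effect is 1.57 and ρ = 0.0032. A continuity correction or unequal clusters also lowers the implied ICC. So 1,767 is reachable with a small ICC, but with none stated it can be neither confirmed nor refuted. I use ρ = 0.005.

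**2. End-line-only precision at 1,750 per arm (m = 175, k = 10).** This is a ceiling for the primary comparison, because the 3,500 includes non-recipient children.

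- V = 0.21 × 0.79 + 0.16 × 0.84 = 0.3003.
- SE² = V[ρ + (1 − ρ)/m]/k = 0.3003 × (0.005 + 0.995/175)/10 = 0.000321, so SE = 1.79 points.
- 5/1.79 = 2.79, and power = Φ(2.79 − 1.96) = 80%. With a t critical value on 18 df it is 75%.
- The within-cluster share of the variance is 0.00569/0.01069 = 53%.

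**3. Adjusting for the child's baseline z-score.** Take the two z-scores as bivariate normal with correlation r, and cut the end-line one at p = 18.5% (midway between 21% and 16%; c = Φ⁻¹(0.185)). The variance of the binary outcome explained by baseline is

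R² = {E[Φ((c − rX)/√(1 − r²))²] − p²} / [p(1 − p)].

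If adjustment acts only within clusters, total variance falls by 0.53 × R².

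| r | R² | Fall in total variance | Power, normal | Power, t (17 df) |
|---|---|---|---|---|
| none | – | – | 80% | 75% (18 df) |
| 0.3 | 0.04 | 2% | 81% | 76% |
| 0.5 | 0.13 | 7% | 83% | 78% |
| 0.6 | 0.20 | 10% | 84% | 79% |
| 0.7 | 0.28 | 15% | 86% | 81% |

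Using 16 df instead of 17 lowers the t figures by about 0.3 points.

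**4. If baseline also explains between-cluster variance.** Replace ρ by ρ(1 − h). With h = 0.5, purely for illustration, variance falls by 26% (r = 0.3) to 38% (r = 0.7). Normal-approximation power is then 90% to 95%.

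**5. Chance imbalance at baseline.** The SD of the between-arm difference is √{2p(1 − p)[ρ + (1 − ρ)/176.7]/10}. A gap of 2.5 points is half the target effect. The value ρ = 0.0043 lies within the range implied in step 1.

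| ρ | Baseline p | SD (points) | P(gap ≥ 2.5 points) |
|---|---|---|---|
| 0.0043 | 12% | 1.4 | 8% |
| 0.0043 | 21% | 1.8 | 17% |
| 0.01 | 12% | 1.8 | 17% |
| 0.01 | 21% | 2.3 | 27% |

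**The case against.** The best defence is that an end-line difference describes when the outcome is assessed, not which covariates are used. A baseline-adjusted GEE is also a test of an end-line difference. The same section promises covariates, the theory-of-change figure is not available here, and a condensed article may leave the list to an analysis plan. This stands to the extent that the article cannot be said to exclude baseline adjustment. It does not remove the point. The article settles how covariates will be picked, from intervention pathways, and that rule neither secures baseline status nor keeps out post-allocation variables. It could name adjusters when it chose to, as it did for the safety test.

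Four stronger readings are tempting, and the document does not support them:

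- **That the primary result would be biased.** Under randomisation the unadjusted contrast is valid, and a standard error that respects clustering already reflects chance imbalance. What is lost is precision and conditional balance.
- **That a material imbalance is likely.** At 8% to 27% for a gap of half the target effect, it is plausible, not probable.
- **That every child has a baseline value.** The article does not say so. Children who reach 6 months between rounds would have none within the eligible age range.
- **That power rises into the nineties, or that the recipient comparison falls short by a known amount.** The first rests on an assumed share of between-cluster variance. The second needs the recipient/non-recipient split, which is not given.

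**Conclusion.** The point holds as a matter of efficiency and prespecification, not validity. The article leaves baseline nutritional status unfixed in the primary model, although the measurement is planned and nothing described in the allocation balances it.

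At ρ of about 0.005 and 1,750 per arm, child-level adjustment is worth about 2% to 15% of the variance: 1 to 6 power points by either reference distribution. At a correlation of 0.3 the child-level gain is negligible; at 0.6 to 0.7 it is useful. Any between-cluster gain comes on top and cannot be sized from the document. The ICC, correlations and baseline prevalence are all assumptions. If an unseen analysis plan already names baseline adjustment, the remaining task is to align the article's wording with it.

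**What to change.** Before end-line data are seen:

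1. Prespecify the child's baseline weight-for-height z-score and the cluster's baseline prevalence as covariates in the primary end-line GEE.
2. State a rule for children without a baseline value, such as a missing indicator.
3. Restrict adjusters in the primary model to variables measured before the intervention. Keep post-allocation pathway variables for the mechanism analyses.
4. Report the marginal prevalence difference in percentage points, the scale of the sample size calculation, and keep the unadjusted result as a sensitivity analysis.

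The cost is analysis wording, one or two between-cluster degrees of freedom out of 18, and the missing-baseline rule. No new data are needed.
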